### Withdrawal of subjects

Participants can cease study treatment at any time for any reason if they wish to do so. Unless they refuse to allow further data collection, such participants will continue to be followed-up and will be analysed in the group to which they were originally allocated. Participants who decline follow-up will have no further trial data collected. Any results collected up to the point at which they decline follow-up will be analysed. Study medication will be discontinued in patients with signs of intrauterine infections or signs of fetal distress (abnormal CTG, meconium stained amniotic fluid). Data of such participants will continue to be analysed. Further management will be left to the expertise of the responsible clinician. The responsible clinician can contact a perinatologist from the project group in case of suspected side effects or other medical problems. If necessary, treatment will be discontinued.

### Monitoring and safety

An independent data safety monitoring board (DSMB) will focus on both effectiveness and safety. Serious adverse events (SAEs) will be collected from the first study-related procedure until 3 months after delivery. All SAEs will be reported to the DSMB within 7 days. Whenever there is proof of effectiveness (at interim analysis) or safety issues (increased (serious) adverse events in one of the two treatment arms) the DSMB will advise whether the trial should be stopped or continued. The DSMB will be blinded when first analysing the data, but unblinded before reaching a decision.

The advice(s) of the DSMB will only be sent to the sponsor of the study. Should the sponsor decide not to fully implement the advice of the DSMB, the sponsor will send the advice to the reviewing Medical Ethics Committee, including a note to substantiate why (part of) the advice of the DSMB will not be followed.

A formal interim analysis is planned after data collection of 500 women. At these interim analyses, the Haybittle-Peto alpha spending function will be used, which means that an effect at interim with a p value <0.001 is considered statistically significant.

### Sample size

Based on the APOSTEL 3 data, the proportion of adverse perinatal outcome in women randomised between 30 and 34 weeks gestation and treated with atosiban was 6%.^10^ Based on two recent studies,^27 28^ we expect a 49,8% reduction of 11.95% adverse perinatal outcome in the placebo group to 6% in the atosiban group. Therefore we need to randomise 722 women (beta-error 0.2; alpha error 0.05). Assuming a 5% drop-out rate, we need to randomise 760 women (380 in each arm).

### Statistical analysis

#### Data analysis

Data analysis will be performed according to the intention-to-treat principle. In the baseline table, categorical variables will be expressed as a number with the percentage of the total allocation arm. Continuous variables will be presented as mean with SD, as geometric mean with 95% CI or as median with IQR, whichever appropriate.

The main outcome ‘adverse neonatal outcome’ will be assessed on the infant level, using a log-binomial generalised estimating equations model to take into account the correlation of outcomes in multiples, resulting in an RR with accompanying 95% CI. To account for stratified randomisation by centre, we will also take centre into the model if the model converges.^29^ We will account for interdependence between outcomes in multiple pregnancies by considering the mother as a cluster variable.^30^

The other secondary outcome measures on the child level will be analysed similar to the primary outcome measure. Outcomes on the maternal level will be assessed by using a binomial regression model with log-link function. When a statistically significant difference in primary outcome is found between both groups, we will calculate the number needed to treat. Time to delivery will be evaluated by Kaplan-Meier estimates and Cox proportional hazard analysis, taking into account the different durations of gestation at study entry, and will be tested with the log rank test. A p value of <0.05 will be considered to indicate statistical significance.

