### Participants/eligibility criteria

Women, aged ≥18 years, with threatened preterm birth and a gestational age between 30^+0^ and 33^+6^ weeks are eligible. Threatened preterm birth is defined as uterine contractions with

A cervical length of <15 mm orA cervical length of 15–30 mm and a positive fibronectin test orIn centres where cervical length measurement is not part of the local protocol: a positive fibronectin test or insulin-like growth factor binding protein-1 (Actim-Partus test) orRuptured membranes.

These inclusion criteria are based on the results and conclusions of the APOSTEL 1 study^20^ and current guidelines within the Netherlands and the UK. Moreover, our previous APOSTEL 3 study, with resembling inclusion criteria, showed that half of the women with these criteria deliver within 7 days,^10^ validating this definition of women at high risk for preterm birth. In addition, the sample size of expected adverse neonatal outcome in the gestational age group of 30–34 weeks, was calculated from the APOSTEL 3 study.

This study was designed in a pragmatic fashion, in order for the results to be applicable in the current clinical practice. As most national guidelines and local protocols propose treatment for threatened preterm birth in both singleton and multiple pregnancies, as well as women with ruptured membranes, all these categories of patients are eligible for the study.

Women with a contraindication for tocolysis, signs of fetal distress, clinical signs of intrauterine infection, previous treatment for threatened preterm birth with corticosteroids in the current pregnancy and known fetal chromosomal or severe structural abnormalities are not eligible.

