### Procedures, recruitment, randomisation and collection of data

Potential participants will be identified by the local research co-ordinators and/or the staff of participating hospitals. Women eligible for the trial will be counselled by doctors, midwifes or research nurses trained in ‘good clinical practice’, and will be given a patient information form to read. Those who wish to participate, will be asked to give for written informed consent and are registered within the central trial database. Randomisation will be performed by using sequentially numbered medication packs available in each centre. Only the independent data manager has access to the computer-generated randomisation list in which the medication numbers are linked with atosiban or placebo. Treatment allocation is blinded to investigators, participants, clinicians and research coordinators. Randomisation will be balanced with varying block sizes of 2 and 4, and stratified by centre.

At study entry, baseline demographic, prior obstetric and medical history will be recorded into the web-based case report form accessible through a secure central website (Castor Electronic Data Capture, Ciwit B.V.).^21^ Details of delivery, maternal and neonatal assessments during pregnancy and postpartum period will be recorded on the same system. All data will be coded, processed and stored with adequate precautions to ensure patient confidentially. This is described in a separate data management plan.

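### The primary model could adjust for gestational age at entry at almost no cost; leaving it out is valid but gives up a little precision and robustness

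*Protocol article*

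**What the plan says.** The Data analysis section of the protocol article fixes most of the primary model. The composite "will be assessed on the infant level, using a log-binomial generalised estimating equations model to take into account the correlation of outcomes in multiples", and the result is an RR with its 95% CI. Clustering is by mother: "We will account for interdependence between outcomes in multiple pregnancies by considering the mother as a cluster variable". One covariate is named, with a condition: "To account for stratified randomisation by centre, we will also take centre into the model if the model converges". Gestational age at entry does not appear.

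The same section treats time to delivery differently. That analysis is done "taking into account the different durations of gestation at study entry, and will be tested with the log rank test".

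Three other places bear on the point:

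- **Eligibility.** Women are included "with threatened preterm birth and a gestational age between 30" weeks and 33 weeks + 6 days, so the value must be known for each of them before randomisation.
- **Randomisation.** The procedures section stratifies by centre only.
- **Subgroup and sensitivity analyses.** Plurality and membrane status are covered by subgroups with interaction tests, and by a sensitivity analysis that excludes both groups. Gestational age at entry is in neither list.

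Further details are left to a separate SAP, to be completed before data lock, which is not at hand.

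**The concern.** Women enter over a four-week window, and the composite consists of death and serious complications in preterm infants. Gestation at entry is therefore a plausible prognostic variable. It is not balanced by design, and the primary model does not adjust for it.

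Two things are at stake. The first is a little precision. The second is the single trial that is actually run: if the arms happen to differ in mean gestation, the unadjusted RR carries that difference, and an adjustment chosen after seeing it is open to challenge as post hoc.

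The planned model may also end up thinner than it looks. About 65 events are expected (361 × 0.1195 + 361 × 0.06 = 43.1 + 21.7 = 64.8). Spread over more than 40 hospitals, that is fewer than two per hospital, so the centre term may well be dropped and leave treatment alone.

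**Working it through.** **Inputs from the article.** Risk 11.95% on placebo and 6% on atosiban (RR 0.06/0.1195 = 0.502); alpha 0.05; power 80%; 722 women, or 760 with 5% dropout; entry window of four weeks (28 days).

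**Assumed, because the article gives no figure.** Entry gestation is uniform over the window. Placebo risk is log-linear in gestation, with a risk ratio per later week of 0.8, 0.7, 0.6 or 0.5, and averages 11.95%. There is one infant per woman and no centre effect.

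**Step 1: the plan's own figure.** Two-proportion formula, two-sided 0.05, pooled variance under the null, mean risk 0.08975:

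n per arm = [1.960 × √(2 × 0.08975 × 0.91025) + 0.842 × √(0.1195 × 0.8805 + 0.06 × 0.94)]² / 0.0595² ≈ 361.1

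This is 722 when rounded to the nearest woman per arm (724 when rounded up), and 722/0.95 = 760. The plan's figures reproduce without any covariate, so the stated power does not depend on adjustment.

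**Step 2: average gain from adjustment.** 1,500 simulated trials of 722 women per gradient, using log-link regression with robust standard errors as a stand-in for the log-binomial GEE, with and without a linear gestation term:

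| RR per week | Placebo risk at start / end of window | Variance of log RR, adjusted / unadjusted | Power, unadjusted | Power, adjusted |
|---|---|---|---|---|
| 0.8 | 18.1% / 7.4% | 0.994 | 79.0% | 79.4% |
| 0.7 | 22.4% / 5.4% | 0.981 | 81.2% | 81.9% |
| 0.6 | 28.1% / 3.6% | 0.960 | 81.5% | 82.9% |
| 0.5 | 35.3% / 2.2% | 0.955 | 80.8% | 82.9% |

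Each power figure has a simulation error of about √(0.8 × 0.2/1500) = 1 point. With no gradient the variance ratio was 1.00, so nothing is lost. In terms of sample size, the gain equals 722 × 0.006 ≈ 4 women to 722 × 0.045 ≈ 32 women. A separate simulation with risk halving weekly, from 25% at 30 weeks to 3% at 33 weeks, gave a variance ratio of 0.945 and power of 79.6% against 82.7%. That sets the upper end of about 3 points.

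**Step 3: effect of a chance imbalance.**

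- SD of the arm difference in mean gestation = (28/√12) × √(2/361) = 8.08 × 0.0744 = 0.60 day. About one trial in 20 differs by 1.96 × 0.60 ≈ 1.2 days or more.
- Shift in the unadjusted RR at 1.2 days: (1/0.5)^(1.2/7) = 1.126, or about 12 to 13%; with 0.7 per week, 6%; with 0.8 per week, 4%.
- Unadjusted SE of log RR = √[0.8805/(361 × 0.1195) + 0.94/(361 × 0.06)] = √0.0638 = 0.253.
- At 0.5 per week the shift is ln 2 × 1.2/7 = 0.119, or 0.47 SE. By normal approximation, power when balanced is Φ(0.689/0.253 − 1.96) = 78%. With the imbalance it is 62% or 89%, depending on direction.

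**Step 4: are steps 2 and 3 separate effects?** No. One SD of imbalance at 0.5 per week contributes (ln 2 × 0.6/7)² = 0.0035 to the variance, and 0.0035/0.0638 = 5.5%. This is the same share that adjustment removes in step 2, seen from one unlucky trial instead of on average.

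**The case against.** The strongest case against the point is that nothing in the article is wrong. Under randomisation, treatment with or without centre gives a valid RR and confidence interval, and chance imbalance is already part of that interval. Covariate choice is often settled in the SAP, which the article announces. The gain is small even at a steep gradient. Accounting for gestation in the time-to-delivery analysis has its own reason, since entry gestation governs how much pregnancy remains. A log-binomial model that may not carry centre could struggle with a further continuous term.

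Most of this stands, and it limits what a reader may infer:

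- **That the primary estimate is biased or its error rate inflated.** It is not, on average over randomisations.
- **That gestation is the strongest predictor, or that risk falls steeply by week.** The article ranks no predictors and gives one rate per arm for the whole window.
- **That a 12% shift in RR is a harm on top of the lost precision.** Step 4 shows that it is the same variance.
- **That the two analyses contradict each other.** They may legitimately differ.

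Two parts of the objection do not dispose of the point. The article states the primary model and its covariate policy, so this concerns a stated choice and not merely an omitted detail. The convergence worry is met by a prespecified log-link Poisson GEE with robust standard errors.

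**Conclusion.** The point holds as a minor, inexpensive improvement. The stated primary model omits a baseline variable that is known for every woman, is not a randomisation stratum, and is used for another outcome. Prespecifying it would lower the variance of the log RR by about 1 to 5%, add about 0 to 3 points of power, and protect the estimate against a chance imbalance in gestation.

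These sizes rest on assumed weekly risk ratios of 0.8 to 0.5, uniform entry gestation, one infant per woman and no centre effect. A weaker gradient brings the gain close to nil. The documents do not support calling the planned analysis invalid, and the sample size needs no change. The unseen SAP may already include the term.

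**What to change.** Before data lock, state the following in the SAP:

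1. The primary infant-level model includes treatment, gestational age at randomisation as a continuous covariate, and centre as planned. Plurality and membrane status at entry are optional additions.
2. If the log-binomial GEE does not converge, a log-link Poisson GEE with robust standard errors clustered on mother is used, with gestational age kept in the model.
3. The model without gestational age (and without any optional covariate added) is reported as a sensitivity analysis.

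The child-level secondary outcomes, which the article analyses in the same way as the primary outcome, can follow the same rule.

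The cost is SAP wording and a slightly more complex model; no new data are needed for gestational age. The adjusted RR is read as common across gestational age. If that holds, adjustment leaves the target unchanged, because a common RR is collapsible. If it does not, the two RRs may differ somewhat, which is a further reason to report both.

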### Subgroup analyses

The following subgroup analyses are planned:

Singleton versus multiple pregnancy.Cervical length <15 mm versus cervical length 15–30 mm and a positive fibronectin test (or no cervical length measurement and a positive fibronectin test or Partus test).Ruptured or unruptured membranes at entry.Previous preterm birth.

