**Methods and analysis:**

We designed an international, multicentre, randomised, double-blinded, placebo-controlled clinical trial. Women with threatened preterm birth (gestational age 30–34 weeks), defined as uterine contractions with (1) a cervical length of < 15 mm or (2) a cervical length of 15–30 mm and a positive fibronectin test or (3) in centres where cervical length measurement is not part of the local protocol: a positive fibronectin test or insulin-like growth factor binding protein-1 (Actim-Partus test) or (4) ruptured membranes, will be randomly allocated to treatment with atosiban or placebo for 48 hours. The primary outcome is a composite of perinatal mortality and severe neonatal morbidity. Analysis will be by intention to treat. A sample size of 760 participants (380 per group) will detect a reduction in adverse neonatal outcome from 11.95% to 6% (alpha error 0.05, beta error 0.2). A cost-effectiveness analysis will be performed from a societal perspective.

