### Sensitivity analysis

A sensitivity analysis will be performed excluding multiple pregnancies and pregnancies complicated by preterm premature rupture of membranes.

To assess whether a subgroup effect is present, we will add an interaction term between the subgrouping variables and the treatment allocation to the regression model. When an interaction term is statistically significant (p<0.05), we will estimate the treatment effect within strata of the subgrouping variable.

Details of the statistical analysis will be describes in separate statistical analysis plan that will be completed before data lock.

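### The cervical-length subgroup pools unmeasured women with the 15–30 mm group, so its interaction test cannot be read as an effect of cervical length

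*Protocol article*

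**What the plan says.** The protocol article, under Subgroup analyses, sets one side of the contrast against the other as "Cervical length <15 mm versus cervical length 15–30 mm and a positive fibronectin test", and adds to the second side, in brackets, "or no cervical length measurement and a positive fibronectin test or Partus test".

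The eligibility criteria show who has no measurement. The third entry route applies "in centres where cervical length measurement is not part of the local protocol: a positive fibronectin test" or a positive Actim-Partus test (abstract, Methods and analysis; repeated under Participants/eligibility criteria). No cervical length is required or excluded on this route.

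Under Sensitivity analysis the article says how subgroups are tested: "we will add an interaction term between the subgrouping variables and the treatment allocation to the regression model". Effects within strata are estimated only if that term has p<0.05. On centre, randomisation is stratified, and under Data analysis "we will also take centre into the model if the model converges". The article states no separate category for unmeasured women and no analysis limited to measured women.

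**The concern.** Take two women with the same cervix below 15 mm and the same positive test. If the centre measures, the woman is in the <15 mm stratum. If it does not, she is in the comparator. Her stratum thus depends partly on centre policy, not only on her cervix.

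Two things follow for the interaction:

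- **Dilution.** Short cervices in the comparator pull a true difference by cervical length towards the null. Cervices above 30 mm can enter the comparator by the same route, with an effect that cannot be signed in advance.
- **Centre practice.** Non-measuring centres contribute only to the comparator. If the effect of atosiban differs between measuring and non-measuring centres for any other reason, that difference appears as a cervical-length interaction.

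At stake is the reading of one subgroup result. A null interaction could be taken as evidence that cervical length does not matter, or a positive one as evidence that it does, when the contrast supports neither statement.

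**Working it through.** **The plan's own figure.** The protocol states no figure for this subgroup. Its overall sample size is not in dispute: 11.95% versus 6%, two-sided 0.05 and 80% power give 362 per arm, or 724 (pooled variance), against 722 stated; 722/0.95 = 760.

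**Inputs.** From the documents: the grouping, the entry routes, the event rates and 380 women per arm. Assumed, because the documents give no values: u, the unmeasured share of the pooled stratum; q, the share of unmeasured women truly below 15 mm; the relative risks (RRs); and equal baseline risk throughout.

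**Step 1: dilution.** With m = u × q, the pooled stratum has RR_pooled = m × RR_short + (1 − m) × RR_long. Attenuation on the log scale is 1 − ln(RR_short/RR_pooled) / ln(RR_short/RR_long).

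| u | q | m | Attenuation, RR 0.5 short and 1.0 long | Attenuation, RR 1.0 short and 0.5 long |
|---|---|---|---|---|
| 0.25 | 0.2 | 0.05 | RR_pooled 0.975: 4% | RR_pooled 0.525: 7% |
| 0.50 | 0.4 | 0.20 | RR_pooled 0.90: 15% | RR_pooled 0.60: 26% |
| 0.75 | 0.4 | 0.30 | RR_pooled 0.85: 23% | RR_pooled 0.65: 38% |

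Middle row, first case: 1 − ln(0.5/0.90)/ln(0.5) = 1 − 0.588/0.693 = 0.15. The calculation leaves out women above 30 mm, and unequal baseline risk would change the weights.

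**Step 2: centre practice.** Suppose cervical length does not modify the effect, but RR is 0.5 in measuring and 1.0 in non-measuring centres. Then RR_pooled = u × 1.0 + (1 − u) × 0.5, and the apparent ratio of RRs is 0.5/RR_pooled:

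- u = 0.2: 0.5/0.6 = 0.83
- u = 0.4: 0.5/0.7 = 0.71
- u = 0.6: 0.5/0.8 = 0.63

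If the RR is the same under both policies, the apparent ratio is 1 and nothing spurious arises. A centre main effect would adjust baseline risk, but not a treatment effect that differs by policy.

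**Step 3: what removing the unmeasured women does to precision.** Take two strata of equal size and variance proportional to 1/n. The interaction variance goes from 1 + 1 to 1 + 1/(1 − u), so the z-value is multiplied by √(2/(1 + 1/(1 − u))): 0.93, 0.82 and 0.63 for u = 0.25, 0.5 and 0.75. Pooling retains 0.96, 0.85 and 0.77 of the log interaction in the first case of Step 1, and 0.93, 0.74 and 0.62 in the second. Restriction therefore brings no dependable gain in power.

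**Step 4: scale against noise.** Expected events are 380 × 0.1195 = 45.4 and 380 × 0.06 = 22.8, about 68 in all. The standard error of the overall log RR is √(1/45.4 + 1/22.8 − 2/380) = 0.25. For an interaction between two equal halves it doubles to about 0.49, and it is larger once women who entered on ruptured membranes fall outside the contrast. The middle-row dilution is 0.15 × 0.693 = 0.10 in the first case and 0.26 × 0.693 = 0.18 in the second.

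**The case against.** The best reply is that the subgroup was never meant as a pure cervical-length contrast. It can be read as entry on ultrasound alone against entry that needed a positive biochemical test, which is coherent in a pragmatic trial, and the article names the unmeasured women openly. This stands as a possible reading. It does not rescue the contrast as a statement about cervical length, which is how its two sides are chiefly described. Nor does it give a clean test-status contrast, since the <15 mm side has no stated test requirement.

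A reader might infer that any difference between strata must partly be a difference between centres or countries. The documents do not support that. An apparent interaction arises only if the treatment effect itself differs by measuring policy, and nothing in the article shows that it does. Measuring centres feed both strata, so the alignment is partial, and the article does not tie measuring policy to country. Randomisation is stratified by centre.

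A reader might also use the simple rule that the log interaction shrinks by u × q, giving 5%, 20% and 30%. That is only an approximation: the RR mixture gives 4%, 15% and 23% if the benefit lies in short cervices, and more than the rule if it lies in the longer ones.

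Materiality is low, as Step 4 shows. A separate analysis plan is promised before data lock and could split the groups. But the article already states the pooling, so this is a stated rule and not an item left open.

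**Conclusion.** The point holds as one of interpretation. The planned interaction cannot be read as a cervical-length effect, because the comparator contains women of unknown length who come only from non-measuring centres. That follows from the text alone.

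The size is unknown. The 4% to 38% dilution rests on assumed shares, a twofold difference in RR and equal baseline risk. The apparent ratios of 0.63 to 0.83 rest on an assumed policy-related difference in effect. Neither set is an estimate for this trial.

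A reader might go further and infer that the within-stratum comparisons are biased, or that the primary result is touched. Neither follows: the grouping is set at baseline, the comparisons within strata remain randomised, and the primary analysis does not use this variable. This is a low-cost improvement to an exploratory analysis.

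**What to change.** In the analysis plan, before data lock:

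1. Define three categories: measured below 15 mm; measured 15–30 mm with positive fibronectin; not measured with a positive fibronectin or Partus test.
2. Base the cervical-length interaction on the two measured categories.
3. Show the unmeasured group separately, with its own event counts and RR, as descriptive.
4. Keep the planned pooled contrast as a secondary display, labelled by entry route and not by cervical length.

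This uses entry data that eligibility already requires and leaves the sample size and primary analysis as they are. The cost is fewer women in the tested contrast, no contribution to it from non-measuring centres, and a less precise interaction estimate. The change should be presented as a gain in interpretability and not in power.
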